**Describe iron metabolism, handling and recycling in full term neonates at birth and during the first 7 days of life.**

Analysis of the longitudinal data will involve generalised estimating equations incorporating time of measurement. We will include spline terms at each time point to evaluate the change in the outcomes (all primary and secondary outcome parameters) over time during the transition period from cord to 24–79; 80–135; 136–192 hours after birth. Note that this will only include data collected from Group D neonates and will not be a comparison between Groups A–C and D neonates.

III. 
**Determine if sera from preterm and low birthweight neonates supports a greater level of
*ex-vivo* growth of microorganisms that are common causes of neonatal sepsis in Africa and The Gambia (
*Staphylococcus aureus, Klebsiella pneumoniae, Escherichia coli, Enterobacter* spp.
*, Enterococcus* spp., and
*S.* Typhimurium) in comparison to sera from FTB+NBW neonates.**

The bacterial growth will be analysed in a similar method as described in [name]
*et al.* (2015)
^53^ in order to determine if changes in iron availability modulate the growth. Growth assays will be fitted to a standard form of the logistic equation:

$$N_{t}=\frac{K}{1+(\frac{K-N_{0}}{N_{0}})e^{-rt}}$$

Here, the population size at the beginning of the growth curve is given by
*N
_0_.* The carrying capacity is given by
*K*. The intrinsic growth rate of the population is
*r*. We will generate the best fitting values of
*K*,
*r* and
*N
_0_* for the growth curve data. Additionally, for each bacterium, we compare the time at which the population density reaches
$\frac{1}{2}K$ (inflection point), the fastest possible generation time (doubling time) and the area under the logistic curve obtained by taking the integral of the logistic equation. This will be used to assess growth curves from different sample types (Cord vs V1) and between the four study groups.

**IV. Characterize frequencies and functionality of neutrophils, monocytes, dendritic cells, NK cells, B cells, T cells (D8 and CD4) in cord blood from full term, premature and low birthweight neonates.**

Exploratory analysis will be conducted using linear regressions modelling.

Statistical analyses will be performed using
STATA (StataCorp. 2017. Stata Statistical Software: Release 15. College Station, TX: StataCorp LLC);
R (R Foundation for Statistical Computing, Vienna, Austria.) and
Data Desk (Data Description Inc Ithaca NY). All files used will have an accompanying data dictionary. Annotated STATA do-files or R files will be used to describe any data transformations and statistical tests used.

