### Study objectives

The primary study objective is to characterize in detail how full term, preterm and low birthweight neonates modulate serum iron in the first 24 hours of life. We hypothesize that premature and/or low birthweight babies have a defect in their ability to sequester iron at 6–24 hours after birth in comparison to full term neonates with normal birthweight.

The secondary objectives are:

I. Characterise how iron metabolism, handling and recycling differs between full term, preterm and low birthweight neonates at birth and during the first 24 hours of life.II. Describe iron metabolism, handling and recycling in full term neonates at birth and during the first 7 days of life.III. Determine if sera from preterm and low birthweight neonates supports a greater level of
*ex-vivo* growth of microorganisms that are common causes of neonatal sepsis in Africa and The Gambia (
*Staphylococcus aureus*,
*Klebsiella pneumoniae*,
*Escherichia coli*, Group B
*Streptococcus*,
*Streptococcus pneumoniae* and
*Salmonella enterica* serovar Typhimurium (
*S.* Typhimurium hereafter)) in comparison to sera from full term, normal birthweight neonates.IV. Characterize frequencies and functionality of neutrophils, monocytes, dendritic cells, NK cells, B cells and T cells (D8 and CD4) in cord blood from full term, premature and low birthweight neonates.

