***Hospital health assessment (study recruitment and group allocation).*** At 6–24 hours post-delivery, recruited mothers and their neonates will be invited to a private consultation with the study research clinician. Further demographic data will be collected, along with a photograph of the antenatal card to gather gestational age data (fundal height, last menstrual period and ultrasound), mother’s last haemoglobin level before delivery (dated), known sickle cell status, neonate immunisations, and medication given to the mother (pre, during and post-delivery) and the neonate. A complete review of systems of the mother and neonate plus anthropometric data on the newborn will then be collected. Neuromuscular and physical maturation of each neonate will be assessed using the New Ballard Score
^48^.

Neonates will be excluded if they score less than 32 weeks of gestation. From this assessment, the neonate will be assigned to a specific study group. If the neonate is allocated to the Group D (FTB+NBW) group, the neonate will be allocated to a randomised bleed group (≥24 hours - <80 hours (Group D1); ≥80 hours - <136 hours (Group D2); and ≥136 - <192 hours (Group D3). Failure to meet the inclusion criteria at this stage of the study protocol, will result in exclusion from the study.

According to current practice, at-birth vaccination of neonates at Kanifing General Hospital (The Gambia), does not occur until a later time point in the first week of life due to social and logistical reasons. However, mothers will still be asked whether the neonate has been vaccinated prior to the health assessment before the 1
^st^ venous bleed takes place. The answers will be recorded and analysed.

***1
^st^ venous blood draw (all neonates).*** A blood sample will be collected from all neonates that have passed the inclusion criteria in the hospital health assessment. Immediately after the health assessment, a venous blood draw will be performed (6–24 hours post-delivery). PTB and/or LBW neonates will donate 2ml of venous blood. FTB+NBW neonates will donate 3.5ml of venous blood. All samples will reach the laboratory within three hours post collection for primary processing.

### Community health assessment and 2
^nd^ venous blood draw

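### The time points listed for the Group D first-week model omit the 6–24 h sample, although the main fall in TSAT is expected by about six hours

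*Protocol article*

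**What the plan says.** Secondary objective II (Study objectives) is to "Describe iron metabolism, handling and recycling in full term neonates at birth and during the first 7 days of life".

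The sampling schedule gives each Group D neonate three occasions:
- Cord blood at delivery.
- A first venous sample (V1). Under Hospital assessment and 1st venous blood draw, the protocol says of all neonates that pass assessment that "a venous blood draw will be performed (6–24 hours post-delivery"), and for Group D that "FTB+NBW neonates will donate 3.5ml of venous blood".
- One second venous sample (V2), in a randomly allocated window: D1 from 24 to under 80 h, D2 from 80 to under 136 h, D3 from 136 to under 192 h.

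The analysis of objective II (Statistical analysis) says "Analysis of the longitudinal data will involve generalised estimating equations incorporating time of measurement". It continues: "We will include spline terms at each time point to evaluate the change in the outcomes", over all primary and secondary outcomes, "during the transition period from cord to 24–79; 80–135; 136–192 hours after birth". It adds: "Note that this will only include data collected from Group D neonates", and that the analysis is not a comparison with Groups A–C.

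**The concern.** The article gives a specific list of time points for this model, and the list does not match its own sampling schedule or its own objective. Spline terms are tied to the time points, so the list governs the shape of the curve as well as describing the data. None of the listed post-birth points comes before 24 h.

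That is the interval where the protocol expects most to happen. The Abstract reports from earlier data in full-term neonates that TSAT drops from 45% in cord blood to about 20% by six hours. A first-week curve built on the list as printed would join cord blood to a window that opens at 24 h, and would spread a fall of a few hours over a day or more. Objective II is the only planned time course within Group D, so no other analysis would supply the missing part of that description.

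**Working it through.** **No figure to reproduce.** The protocol gives no sample size or power for objective II; power was not calculated for secondary outcomes. The check is a comparison of texts, with two calculations for scale.

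**Step 1. Schedule against list.**

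| Group D sample | Age | Who | Listed for objective II? |
|---|---|---|---|
| Cord | 0 h | all | yes |
| V1 | 6–24 h | all | **no** |
| V2, D1 | 24 to <80 h | random third window group | yes (24–79) |
| V2, D2 | 80 to <136 h | random third window group | yes (80–135) |
| V2, D3 | 136 to <192 h | random third window group | yes (136–192) |

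The three listed post-cord windows are the V2 windows, each 56 h wide (80 − 24, 136 − 80, 192 − 136). V1 is the only scheduled sample absent. The analysis text for objective III does name cord against V1, so the authors name V1 where they describe its use.

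**Step 2. Sampling occasions.** Group D has 300 neonates (Sample size and power).
- With V1: 3 × 300 = 900.
- Without V1: 2 × 300 = 600.
- Difference: 300, one third, which would include every Group D observation between birth and 24 h.

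**Step 3. What the curve would read at 6 h if V1 did not enter.** The protocol gives no TSAT value after 24 h, so the later value is an assumption. Let the curve start at 45% at 0 h and reach x% at the first later observation, at t hours. A straight line gives

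TSAT(6) = 45 − (45 − x) × 6/t.

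- x = 20, t = 51.5 (midpoint of 24–79): 45 − 25 × 6/51.5 = 42.1%.
- x = 30, t = 51.5: 45 − 15 × 6/51.5 = 43.3%.
- Lowest in the range tried (x = 15, t = 24): 45 − 30 × 6/24 = 37.5%.
- Highest in the range tried (x = 30, t = 79): 45 − 15 × 6/79 = 43.9%.

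So the line reads about 38–44% at 6 h, against about 20% in the Abstract.

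**Step 4. If V1 data enter but no knot is added.** The first spline term after birth would then sit at 24 h or later. With a linear spline, one straight segment would have to cover a drop by six hours and whatever follows up to 24 h. A segment from 45% at 0 h to an assumed 20% at 24 h reads 45 − 25 × 6/24 = 38.8% at 6 h. A least-squares fit would not pass through those two points, and a higher-degree spline could bend, so this shows the direction of the problem and is not a prediction. Including V1 and placing a knot early are separate needs.

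**The case against.** The strongest reply is that the protocol nowhere excludes V1. A model that uses the time of measurement and draws on Group D data is compatible with V1 being in it, and the listed transition can be read as a span from birth to each end window, with V1 inside. In a condensed article this may be no more than an incomplete list. That stands: a planned exclusion is an inference, not something the text says. It does not remove the need to correct the list, because the spline terms are attached to the listed points.

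A reader might infer that the study as a whole misses the early drop in iron. The documents do not support that. The primary analysis compares TSAT and serum iron at 6–24 h between groups, unadjusted and adjusted for cord level, and objective I covers the first 24 h by a similar strategy. What those analyses do not give is a time course within Group D.

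A reader might also infer that time is handled only in windows. The sentence on GEE says that time of measurement is incorporated, so that does not follow. Nor does it follow that D3 overruns the objective: whether 168–192 h lies beyond day 7 or is day 7 depends on a counting convention that is not stated. GEE with splines is a standard choice, and this point gives no reason to replace it.

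It is fair, too, that the figures in steps 3 and 4 use straight lines where the plan has splines, and assumed values after birth. They are illustrations only.

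**Conclusion.** The point holds in a limited form and should be corrected. The list of time points for the Group D first-week model leaves out 6–24 h, which the schedule samples in every Group D neonate and which lies within objective II. Followed as printed, the curve has no spline term, and possibly no data, between 0 and 24 h, and it would misplace the early fall in time.

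The size depends on what was intended. If V1 is excluded, 300 of 900 occasions drop out of this one model, and the illustrated reading at 6 h is about 38–44% rather than about 20%. This assumes 15–30% at a first later observation somewhere in 24–79 h. If V1 is included and only the list is incomplete, what remains is the absence of a knot before 24 h. Either way the effect is confined to a descriptive, exploratory trajectory; the primary comparison is untouched.

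The correction has limits. V1 starts at 6 h, so the curve between 0 and 6 h stays an interpolation, and one V1 per neonate does not locate an individual lowest point.

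**What to change.** In the analysis text for secondary objective II:
- State that the model uses all Group D samples: cord at 0 h, and V1 and V2 each at its exact age in hours.
- Change the list of time points to cord, 6–24, 24–79, 80–135 and 136–192 h.
- Specify at least one spline knot inside the first 24 h, placed with regard to V1 starting at 6 h.
- If V1 was meant to be left out of this model, say so and give the reason.

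The cost is a change of wording in the protocol or analysis plan, best made before the data are analysed. The samples are already scheduled, so no new bleed, visit or assay is needed.

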### Dissemination of findings

The study results will be published in relevant peer-reviewed journals and key findings will be presented at international scientific meetings. Data sharing will be in agreement with the sponsor policy on research data sharing and with the Bill & Melinda Gates Foundation Global Access requirements.

### Study status

The study is in the data collection phase.

## Discussion

Humans and bacteria are involved in an on-going tug of war over iron. Each side has evolved complicated and varied iron-acquisition mechanisms in an effort to turn the tide of war in their own favour
^55^. Nutritional immunity describes the processes by which the human host tries to starve invading organisms of nutrients, especially iron.

This study aims to determine if premature and low birthweight babies have a defect in their ability to sequester iron during the first 24 hours of life. The study design will produce a detailed and extensive picture of iron metabolism in neonates. To our knowledge, no other study has tried to analyse such a large and diverse collection of iron and infection variables in neonates born in Sub Saharan Africa. The study will enrol subjects who are all at an increased risk of neonatal infection, and subsequent sepsis and death.

A potential limitation of this study is the inadequacy of using the New Ballard Score as the only method of gestational aging. Original and New Ballard Score are reported to overestimated gestational age compared to ultrasound and in particular, misclassify preterm infants as term newborns
^56^. Additionally, newborn clinical assessments as a whole, tend to underestimate gestational age in growth-restricted neonates
^56^. The gold standard of gestational aging is an ultrasound in the first trimester
^57^. However, this procedure is rarely correctly completed in this study population. If it is documented on the mother’s antenatal records, care will be taken to record it. Limits of the study also include that HIV status, TB status and iron supplementation given are all gained from the antenatal records of the mother. Furthermore, antenatal records will not contain all information on medication given in every mothers’ pregnancy. As a result, care will be made to extensively question participants mother’s during verbal one-to-one consultation with our study research clinician.

In conclusion, our overarching study goal is to evaluate the likelihood that novel products designed to induce hypoferremia (potentially via mini-hepcidins
^58^) may be useful in the future for the prevention of neonatal sepsis in high risk babies. This could be produced by a transient redistribution of iron away from the circulation, thus applying a bacteriostatic brake on any bacteria that have crossed into the baby’s systemic circulation and hence boosting host survival in vulnerable newborns. We hope this may ultimately help reduce the use of antibiotics in maternal and neonatal wards worldwide.

## Ethical approval

This study has been approved by The Gambia Government/MRC Joint Ethics Committee (no. SCC1525) and Ethics Committee of London School of Hygiene and Tropical Medicine (ref no. 14316). The study procedures will be explained to the neonate’s mother/guardians orally or in writing. A neonate is only recruited into the study after the consent form has been signed/thumb printed by the mother/guardian.

This study was registered with clinicaltrials.gov (
NCT03353051) on 27 November 2017.

## Data availability

### Underlying data

No data are associated with this article.

### Extended data

Figshare: [name]
*et al.* GatesOpen Research SCC1525v2__NeoInnate_Participant Info&Consent form Route 1.
https://doi.org/10.6084/m9.figshare.8069195.v4
^49^

This project contains the following extended data:

SCC1525v2__NeoInnate_Consent form Route 1_v3 Approved8Nov17.docx (Route 1 consent and information sheet)

Figshare: [name]
*et al.* GatesOpenResearch SCC1525v2_NeoInnate_Consent form Route 2_Part 1_ (Umbilical Cord Blood Collection) - Labour Ward_v1.1-Approved 8Nov17.
https://doi.org/10.6084/m9.figshare.8069246.v1
^50^

This project contains the following extended data:

SCC1525v2_NeoInnate_Consent form Route 2_Part 1_ (UCB Collection) - Labour Ward_v1.1-Approved 8Nov17.docx (Route 2 consent and information sheet part 1)

Figshare: [name]
*et al.* Gates Open Research SCC1525v2__NeoInnate_Consent form Route 2_Part 2_(Post-Delivery) - ANC Outside SGH v1-Approved 8Nov17.
https://doi.org/10.6084/m9.figshare.8069243.v1
^51^

This project contains the following extended data:

SCC1525v2__NeoInnate_Consent form Route 2_Part 2_(Post-Delivery) - ANC Outside SGH v1-Approved 8Nov17.docx (Route 2 consent and information sheet part 2)

Data are available under the terms of the
Creative Commons Attribution 4.0 International license (CC-BY 4.0).
